## Abstract

**Background:**

Critical to efforts to end the HIV epidemic is the identification of persons living with HIV who have yet to be diagnosed and engaged in care. Expanded HIV testing outreach efforts need to be both efficient and ambitious, targeting the social networks of persons living with HIV and those at above-average risk of undiagnosed HIV infection. The ubiquity of mobile phones across many high HIV prevalence settings has created opportunities to leverage mobile health (mHealth) technologies to engage social networks for HIV testing outreach, prevention, and treatment.

**Objective:**

The purpose of this study is to evaluate the acceptability and efficacy of a novel mHealth intervention, “Confidential Social Network Referrals for HIV Testing (CONSORT),” to nudge at-risk individuals to test for HIV using SMS text messages.

**Methods:**

We will conduct the CONSORT study in Moshi, Tanzania, the commercial center and administrative capital of the Kilimanjaro Region in northern Tanzania. After qualitative formative work and pilot testing, we will enroll 400 clients presenting for HIV counseling and testing and 200 persons living with HIV and receiving care at HIV care and treatment centers as “inviters” into a randomized controlled trial. Eligible participants will be aged 18 years or older and live, work, or regularly receive care in Moshi. We will randomize inviters into 1 of 2 study arms. All inviters will be asked to complete a survey of their HIV testing and risk behaviors and to think of social network contacts who would benefit from HIV testing. They will then be asked to whom they would prefer to extend an HIV testing invitation in the form of a physical invitation card. Arm 1 participants will also be given the opportunity to extend CONSORT invitations in the form of automated confidential SMS text messages to any of their social network contacts or “invitees.” Arm 2 participants will be offered physical invitation cards alone. The primary outcome will be counselor-documented uptake of HIV testing by invitees within 30 days of inviter enrollment. Secondary outcomes will include the acceptability of CONSORT among inviters, the number of new HIV diagnoses, and the HIV risk of invitees who present for testing.

**Results:**

Enrollment in the randomized controlled trial is expected to start in September 2024. The findings will be disseminated to stakeholders and published in peer-reviewed journals.

**Conclusions:**

If CONSORT is acceptable and effective for increasing the uptake of HIV testing, given the minimal costs of SMS text reminders and the potential for exponential but targeted growth using chain referrals, it may shift current practices for HIV testing programs in the area.

**Trial Registration:**

ClincalTrials.gov NCT05967208; https://clinicaltrials.gov/study/NCT05967208

**International Registered Report Identifier (IRRID):**

PRR1-10.2196/55068

## Introduction

### Background

The Joint United Nations Programme on HIV/AIDS (UNAIDS) set for 2030 the ambitious 95-95-95 target: diagnosing 95% of all persons living with HIV, initiating antiretroviral therapy for 95% of those diagnosed, and achieving viral suppression for 95% of those treated. Traditional testing approaches have linked countless persons living with HIV to treatment; however, the cost-effectiveness of these approaches for reaching incrementally harder-to-reach persons living with HIV is declining. The 2022 Tanzania Demographic and Health Survey and Malaria Indicator Survey (TDHS-MIS) found that only 79.6% of Tanzanian women and 64% of Tanzanian men had tested for HIV during their lifetime [1]. Furthermore, despite the recommendation that those in the general population who test negative retest annually, only 36.5% of women and 30.6% of men reported testing for HIV in the previous 12 months. Thus, novel approaches that efficiently reach at-risk individuals are urgently needed.

Social and sexual networks play a critical role in HIV transmission [2], testing decisions [3,4], linkage to care [5], and adherence [6]. However, numerous barriers, including HIV-related stigma, legal concerns, and the risk of unwanted serostatus disclosure, can impede HIV-related communication within social and sexual networks [7,8]. The ubiquity of mobile phones across many high HIV prevalence settings, including those in low- and middle-income countries (LMICs), has created opportunities to leverage mobile health (mHealth) technologies to engage social networks along the HIV care continuum for contact tracing, partner notification, clinic engagement, adherence reminders, and support for persons living with HIV [9-11]. The privacy and confidentiality afforded by novel applications of mHealth technologies can help address stigma and legal concerns, and broadly improve the uptake of HIV testing.

This study describes the protocol for a randomized controlled trial (RCT) to evaluate the acceptability and efficacy of mobile phone–based “nudges” in the form of “Confidential Social Network Referrals for HIV Testing” (CONSORT) to reach high-risk individuals and encourage them to test for HIV. The study will adapt and use an existing, highly versatile mobile phone–based appointment reminder and incentive system (mParis) [12-14]. mParis resides in Tanzania and can autonomously send large numbers of SMS text messages according to prespecified algorithms, making it a low-cost tool that can easily be adapted and scaled. In previous work, we explored the hypothetical acceptability and efficacy of CONSORT [15]. The survey results from this work suggested high feasibility and moderate acceptability of CONSORT*.* This study will explore the actual acceptability and efficacy of the intervention.

This study aligns with Tanzania’s 2017-22 “Health Sector HIV and AIDS Strategic Plan (HSHSP-IV),” which listed as its first challenge that HIV testing services need to be more efficient and ambitious [16]. Acknowledging the unfinished business from HSHSP-IV, the “Health Sector Strategic Plan July 2021–June 2026” highlights persistently low rates of HIV testing for some groups, particularly men and young people [17]. If CONSORT is shown to be acceptable and effective, confidential, digital, chain-referral methods could greatly improve the reach and cost-effectiveness of HIV testing efforts. While the CONSORT system will be developed and tested using SMS text messaging in a low-resource setting, the confidential chain-referral approach and the system’s open-source architecture may be extended to promote other health behaviors across varied social networks, app-based technologies, health conditions, and geographic settings.

### Study Aims and Hypothesis

This study aims to evaluate the acceptability and efficacy of automated confidential SMS text messaging–based HIV testing invitations as a means of “nudging” individuals to test for HIV. The overall study hypothesis is that an automated confidential referral system, developed and deployed in the Kilimanjaro Region of Tanzania, will be acceptable to both index participants (inviters) and their referrals (invitees), and it will be effective for increasing uptake of HIV testing. 

### The CONSORT Intervention

The CONSORT process is shown in Figure 1. A consented inviter completes an HIV risk assessment and a survey of their social and sexual network contacts. Next, the inviter selects invitation messages from a menu of options to send to any of their network contacts who they think could benefit from HIV testing. Invitee phone numbers and SMS text messages are transferred securely to mParis. mParis autonomously sends the invitation SMS text message with a unique referral code to each invitee phone number. Invitees presenting for HIV testing with a referral code (invitee testers) will be offered the opportunity to become inviters (Figure 1).

**Figure 1 figure1:**
[figure not shown]
The Confidential Social Network Referrals for HIV Testing (CONSORT) process. (A) A consented “inviter” volunteers the phone numbers of social network contacts and (B) selects the invitation SMS text message. (C) A secure autonomous digital health system sends the selected SMS text messages to each “invitee” phone number. (D) An invitee responding to the invitation presents for HIV testing (“invitee tester”) and is offered the opportunity to become an inviter. mParis: mobile phone–based appointment reminder and incentive system.

## Methods

### Study Setting

The study will be conducted in Moshi, Tanzania. Moshi is the commercial center and administrative capital of the Kilimanjaro Region in northern Tanzania and has an estimated population of about 535,000 [18]. Moshi has 25 HIV counseling and testing (HCT) facilities that offer free HIV testing; many of these function as HIV care and treatment centers (CTCs), providing free HIV care to persons living with HIV [19]. HCT and CTC facilities with adequate volume to support the proposed study activities will be eligible to participate in the recruitment of inviters for the RCT. The uptake of HIV testing among invitees will be assessed across all HCT facilities in the study area.

### Study Sample

The RCT will include gender-balanced samples of 600 inviters, including 400 adult HCT clients and 200 adult persons living with HIV receiving care at participating CTCs.

### Inclusion and Exclusion Criteria

Eligible participants will be aged 18 or older and live, work, or regularly receive care in Moshi. Minors (<18 years) will be excluded, as it will not practically be possible to obtain assent to minors’ participation in a research study from a legal guardian.

### Recruitment

Clients presenting for HIV testing and persons living with HIV and receiving care at participating facilities will be approached consecutively for eligibility determination and informed consent and offered enrollment in the RCT. Recruitment will continue until the target sample sizes have been reached.

### Study Design

The study will evaluate the acceptability and efficacy of CONSORT*.* Because CONSORT may be a substitute for other referral options (eg, word-of-mouth referrals), full attribution of testing uptake to CONSORT would likely overstate the system’s effectiveness. To derive valid estimates of the effect of CONSORT, we will evaluate CONSORT in the context of a traceable substitute referral option: physical invitation cards.

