#### Design of the RCT

The design of the 2-arm RCT is shown in Figure 2. Arm 1 participants will be offered to extend CONSORT invitations or physical invitation cards to any of their network contacts. Arm 2 participants will be offered physical invitation cards alone. Arm 1 represents the intervention arm; Arm 2 represents the active control arm.

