**Figure 2 figure2:**
[figure not shown]
The design of the 2-arm randomized controlled trial (RCT). This RCT with 600 adult inviters will be conducted in Moshi, Tanzania. The primary outcome of interest is the uptake of HIV testing among invitees, defined as the number of invitees testing for HIV within 30 days of enrollment of the inviter per 100 inviters. While not all process elements can be observed, the RCT results yield an unbiased estimate of the efficacy of the Confidential Social Network Referrals for HIV Testing (CONSORT) for the primary outcome: inducing additional persons to test for HIV relative to physical invitation cards alone.

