#### Assessment of Primary Outcome

The primary outcome measure is counselor-documented uptake of HIV testing by invitees within 30 days of the enrollment of the inviter. All clients presenting for HIV testing will be asked if they received an HIV testing invitation by SMS text message or a physical invitation card. Counselors will document referral codes from SMS text messages and collect invitation cards. Referral codes will be validated against a database of referral codes issued. A match is interpreted as an invitee presenting for HIV testing.

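### The card control removes background testing from the arm difference only if both arms deliver equal numbers of invitations and these are shown equally often, so the difference cannot be read as additional persons induced to test

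*Protocol article*

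**What the plan says.** Study Design recognises that crediting all testing to CONSORT would overstate its effect, because SMS may replace other referral routes. Its answer is the card comparator: "To derive valid estimates of the effect of CONSORT, we will evaluate CONSORT in the context of a traceable substitute referral option".

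The arms differ in the channels on offer (Design of the RCT): "Arm 1 participants will be offered to extend CONSORT invitations or physical invitation cards to any of their network contacts", whereas "Arm 2 participants will be offered physical invitation cards alone". SMS are sent automatically once the inviter has supplied numbers and chosen messages (The CONSORT Intervention). Cards depend on the inviter handing them over, which is known only from self-report by phone at 30 days (Phone-Based Follow-Up Survey).

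The primary outcome is "the number of invitees testing for HIV within 30 days of enrollment of the inviter per 100 inviters" (Figure 2 caption). It is modelled per inviter (Analysis of the Primary Outcome). Ascertainment is by code or card: all "clients presenting for HIV testing will be asked if they received an HIV testing invitation by SMS text message or a physical invitation card", and "A match is interpreted as an invitee presenting for HIV testing" (Assessment of Primary Outcome).

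The Figure 2 caption then describes the result as an unbiased estimate of efficacy for "inducing additional persons to test for HIV relative to physical invitation cards alone". On ordinary testing, Background reports that "only 36.5% of women and 30.6% of men reported testing for HIV in the previous 12 months".

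**The concern.** The comparator deals with substitution between referral routes. People who would have tested in the 30-day window without any invitation are a different matter. Such a person enters the count if an invitation reached them and they show it, and does not exist for the trial otherwise. Because the count is per inviter, it rises with the number of contacts who carry a code or card, even if no invitation changes anyone's behaviour.

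Randomisation does not remove this, since the number of contacts invited is itself a consequence of the arm. Arm 1 has arm 2's channel plus a second one that does not depend on handing over a card. If it therefore reaches more contacts, the arm difference mixes induced testing with labelled background testing. Limitations and Considerations mentions only under-counting: tests outside the area and undisclosed invitations.

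At stake is the causal claim, and with it the conclusion about efficacy. The count of new diagnoses per 100 inviters rests on the same matched testers and carries the same ambiguity.

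**Working it through.** **Is there a figure in the plan to reproduce?** The article gives no figure for background testing among contacts or for invitations per inviter. The nearest figures are the detectable differences under Statistical Power: 7, 10, 13, 15, 16 (90%) and 6, 8, 10, 11, 13 (80%) for 20 to 100 arm 2 testers. No two-sample or one-sample Poisson power formula that was tried reproduces them. They match 1.645 × √N (7.36, 10.40, 12.74, 14.71, 16.45) and 1.2816 × √N (5.73, 8.11, 9.93, 11.46, 12.82), which are half-widths of 90% and 80% intervals for a single count. They are not used as a yardstick below.

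**Inputs**
- From the article: annual testing of 36.5% (women) and 30.6% (men), midpoint 33.55% (Background); 600 inviters in about equal arms, so 300 per arm.
- Assumed: these rates apply to contacts, evenly over the year; k extra delivered invitations per arm 1 inviter; c, the share of background testers who use a study facility and show the code or card; two-sided 5% test of two Poisson counts.

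**30-day background probability**, 1 − (1 − p)^(30/365):
- p = 0.306: 0.0296
- p = 0.3355: 0.0330
- p = 0.365: 0.0366

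**Spurious testers in arm 1** = 300 × k × 0.033 × c. **Chance of a significant result favouring CONSORT** when the extra SMS induce nobody and arm 2 has 40 testers = Φ(s / √(80 + s) − 1.96), with s rounded:

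| k | c | s | s / √(80 + s) | Chance |
|---|---|---|---|---|
| 0, equal showing | any | 0 | 0 | 2.5% |
| 1 | 0.5 | 4.95, about 5 | 5/√85 = 0.54 | 8% |
| 1 | 1 | 9.9, about 10 | 10/√90 = 1.05 | 18% |
| 2 | 1 | 19.8, about 20 | 20/√100 = 2.00 | 52% |

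**Range.** With k = 1 and c = 1, a background probability of 1% gives 300 × 0.01 = 3 spurious testers; 5% gives 15.

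**Case with no induced testing in either arm.** If nobody is induced by SMS or card and every invitation is shown, the expected rate ratio equals the ratio of invitations, whatever the background rate. One against one invitation per inviter gives 9.9 v 9.9 testers. One against two gives 9.9 v 19.8, with a two-sided rejection probability of about 44%.

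**The case against.** The strongest reply is that the active control already differences out background testing. Cards label background testers too, and both arms choose contacts from the same prompts (Social Network–Based HIV Testing Invitations). If arm 2 inviters deliver as many invitations and these are shown as often, nothing is left over. That is correct, and it is why the point is conditional.

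Several limits on size also stand:
- The article gives no invitation counts, so k is an assumption. Study Design itself expects some substitution, and the Introduction reports only moderate acceptability in the earlier survey.
- The national rates are self-reported, and Background does not say those tests were uninvited. Contacts chosen because they would benefit from testing may test less often than the average adult.
- Analytic Considerations stratifies by cohort unless pooling is supported. Splitting 40 testers and 10 spurious ones 2:1 gives 6.67/√60 = 0.86, or about 14% for HCT inviters, and 3.33/√30 = 0.61, or about 9% for CTC inviters, instead of 18%.

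Stronger readings are tempting. A reader might infer that the randomised comparison is invalid. It is not: the comparison of documented invitee testers per inviter is sound for what it measures. A reader might infer that the bias certainly favours CONSORT, or depends only on invitations issued. Neither follows. It depends on invitations delivered and shown, and if codes and cards are shown at different rates, the error can go either way even with equal numbers.

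None of this rescues the caption, which states without condition a property that the outcome definition does not guarantee.

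**Conclusion.** The concern holds in conditional form. The trial estimates the difference in documented invitee testers per 100 inviters. That equals additional persons induced to test only if labelled background testing is the same in both arms, and nothing in the article secures this.

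If arm 1 delivers one to two more invitations per inviter, about 5 to 20 of its testers would be spurious, and the chance of a falsely favourable result would be about 8% to 52% rather than 2.5%. This rests on 3.3% background testing per 30 days, 300 inviters per arm, 40 arm 2 testers, half to all of the background testers showing the code or card, and Poisson counts. With equal delivery and equal showing, the excess is zero. The existence of the gap follows from the documents; its size does not.

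**What to change.** Keep the primary count and the design.

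1. **Wording and reporting.** In the Figure 2 caption, replace the claim of an unbiased estimate of induced testing with the difference in documented invitee testers per 100 inviters. Report by arm the SMS sent, the cards issued and the cards reported as distributed.
2. **Tipping-point sensitivity analysis, pre-specified.** From each arm's count, subtract b × (SMS sent + cards reported as distributed), where b is the 30-day probability that a contact tests anyway and shows the code or card, from 0 to 3.7%. Repeat with cards issued as a bound, and with b allowed to differ between SMS and cards. Report the b at which the 95% confidence interval of the arm difference first includes zero. Call the difference additional testers only if the interval excludes zero across the whole range.

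Cards issued should not be the main input, because an undelivered card labels nobody. With 300 issued, half delivered and b = 3.3%, subtracting on issue removes 9.9 arm 2 testers when at most 150 × 0.033 = 5.0 could be background, which favours CONSORT.

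To illustrate, 60 v 40 testers with 600 extra arm 1 invitations gives 20 ± 1.96 × √100, a lower limit of 0.4, and a tipping b of 0.4/600 = 0.07%.

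The cost is a paragraph of analysis text and a revised caption, using data the trial already plans to collect. A counselor question on whether the client had already planned to test is optional. The downsides are that invitation numbers arise after randomisation and card distribution is self-reported, so this can only be a sensitivity analysis, and the claim may become less favourable.

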#### Design of the RCT

The design of the 2-arm RCT is shown in Figure 2. Arm 1 participants will be offered to extend CONSORT invitations or physical invitation cards to any of their network contacts. Arm 2 participants will be offered physical invitation cards alone. Arm 1 represents the intervention arm; Arm 2 represents the active control arm.

**Figure 2 figure2:**
[figure not shown]
The design of the 2-arm randomized controlled trial (RCT). This RCT with 600 adult inviters will be conducted in Moshi, Tanzania. The primary outcome of interest is the uptake of HIV testing among invitees, defined as the number of invitees testing for HIV within 30 days of enrollment of the inviter per 100 inviters. While not all process elements can be observed, the RCT results yield an unbiased estimate of the efficacy of the Confidential Social Network Referrals for HIV Testing (CONSORT) for the primary outcome: inducing additional persons to test for HIV relative to physical invitation cards alone.

#### Assignment to Study Arms

Participant IDs will be randomly assigned to either arm 1 or arm 2 using a random number generator. The random assignment is expected to result in approximately equal numbers of participants in each study arm.

#### Blinding

Neither participants nor research staff will be blinded with respect to inviters’ study arm assignments.

### Primary Outcome

The primary outcome is counselor-documented uptake of HIV testing among invitees within 30 days of the enrollment of the inviter. For invitees who present for HIV testing (invitee testers) after a CONSORT invitation, referral codes, alphanumerical codes that are unique to the phone number of the invitee, will be documented by counselors in logbooks; for invitees presenting with physical invitation cards, counselors will collect the invitation cards.

### Secondary Outcomes

Secondary outcomes include the acceptability of CONSORT among inviters, the number of new HIV diagnoses, and the HIV risk among invitee testers. The assessments of secondary outcomes are detailed later on in their own section.

### Study Activities

#### Enrollment Survey

Participants will complete an interviewer-administered enrollment survey to assess their HIV serostatus, HIV-related behaviors (eg, HIV prevention behaviors, HIV testing history, number of partners, and concurrency) [20], and stigma [21-23], as well as key demographic, socioeconomic, and household characteristics that may correlate with the acceptability and efficacy of CONSORT [24,25]. Surveys will be conducted in Kiswahili. The data will be captured electronically using tablet devices.

#### Social Network–Based HIV Testing Invitations

The enrollment survey will include a survey of inviters’ preferences for extending HIV testing invitations within their social networks. Participants will be asked to think of social network contacts across multiple network dimensions, including partners, family members, friends, coworkers, and other people who are aged 18 years or older and who would benefit from HIV testing. Participants will be asked to whom they would prefer to extend an HIV testing invitation through a physical invitation card; arm 1 participants will also be able to select CONSORT invitations. At the end of the survey, inviters will be given the respective number of coded invitation cards, and arm 1 inviters will be able to send CONSORT invitations to their network contacts (Figure 1).

